### Baseline and Follow-up Measures and Data Collection

Table 2 shows a complete list of study measures and the data collection schedule. The time commitment of participants is approximately 2 hours 45 minutes at baseline (for completing the initial screen, baseline questionnaire, BV1 and BV2), 45 minutes for the 3-month assessment, and 1 hour 30 minutes each for the 6-month and 15-month assessments.

**Table 2 T2:** List of measures and data collection schedule

		Follow-up Month		
	Baseline	3	6	15
**Clinical Measures**				
Height	X			
Weight	X	X	X	X
Waist circumference	X	X	X	X
Blood pressure	X	X	X	X
Fasting blood: Total cholesterol, LDL-C, HDL-C, triglycerides, glucose, hemoglobin A1c	X		X	X
C-reactive protein (CRP)	X			X

**Questionnaires**				
Demographics	X			
Family medical history	X			
Three-day food record	X	X	X	X
Eating Habits Confidence Survey	X	X	X	X
Social Support and Eating Habits Survey	X	X	X	X
Stanford Seven-day Physical Activity Recall	X	X	X	X
Exercise Confidence Survey	X	X	X	X
Social Support and Exercise Survey	X	X	X	X
Smoking and alcohol consumption	X			X
12-item Short Form Health Survey (SF-12)	X	X	X	X
Obesity Related Problems Scale	X	X	X	X
Nine-item Patient Health Questionnaire (PHQ-9)	X	X	X	X
Depression Anxiety Stress Scale	X	X	X	X
Symptoms	X	X	X	X
Adverse events		X	X	X
Medication use	X	X	X	X
Care at non-PAMF health care facilities	X	X	X	X
Unified Theory of Acceptance and Use of Technology^1^		X	X	X
**Data extracted from PAMF electronic databases**				
Current medical problems	X			X
Medications prescribed	X			X
Health care utilization	X			X
PCP characteristics	X			

^1^Questionnaire administered to participants in the SM and CM interventions only

Abbreviations: HDL-C, high-density lipoprotein cholesterol; LDL-C, low-density lipoprotein cholesterol; PCP, primary care provider.

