### Randomization and Blinding

Participants are randomized on a 1:1:1 basis to one of three arms: UC, SM, or CM. Pocock's "minimization" procedure [26] is used to assure better than chance group balance with respect to participant age, gender, race, BMI, fasting blood glucose, waist circumference, and use of PAMFOnline, which is PAMF's online patient portal to access his or her own health record (user vs. non-user). For each participant about to be randomized, a computerized randomization algorithm automatically calculates an imbalance score for each of the balancing factors, as the excess or deficit of previously randomized participants in each arm matching the current patient on that factor. These scores are summed over factors to form a total imbalance score, S, for each treatment arm. The randomization probability of assigning the patient to the treatment associated with the smallest S is set to 2/3, and the other two treatments are each assigned a probability of 1/6 based on Efron's biased coin method [27].

A designated research staff member who is not involved in follow-up data collection or data analysis assigns each study arm a non-revealing label, e.g., A, B, or C, and performs actual randomization of the participants. These labels are used in all study documents and other materials to ensure blinding of the investigators and staff responsible for follow-up data collection and analysis to participant treatment assignments throughout the trial.

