### Data Management

All study data are entered into computerized data files utilizing: 1) Microsoft Access for participant tracking and intervention data entry, 2) Vovici's survey software (Dulles, VA) for self-administered questionnaires and entry of clinical measurements, 3) Food Processor, v8.7 (ESHA Research, Oregon) for nutrient analysis based on three-day food records, and 4) a custom-designed web application for seven-day physical activity recall data entry. Research assistants (blinded to treatment assignment) will review participant responses on questionnaires with participants present, and skipped or incorrectly addressed items will be brought to the participant to correct. All of the data entry systems employ automatic, real-time range, logic, and missing value checks. Data sets will be cleaned, verified and archived, and then read into SAS (Enterprise Guide 4.1; SAS Institute, Cary, NC) data sets, which also are archived. One official copy of all the study data and a master data dictionary are maintained and updated regularly by the study data analyst. All analytic and tracking database files are stored in a secure network drive with daily backups. One copy of the backups is saved on-site and one off-site. Separate archival databases are permanently maintained. The data files can be shared by authorized study personnel both on-site and in remote locations via a secure virtual private network. Multiple levels of password protection are utilized to ensure data security.

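### A questionnaire given only to the two intervention arms, within a review by blinded research assistants, tells those assistants who is in usual care

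*Protocol article*

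**What the plan says.** Four parts of the protocol article bear on this.

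- **Randomization and Blinding.** A designated staff member "assigns each study arm a non-revealing label, e.g., A, B, or C". The purpose is then stated: "These labels are used in all study documents and other materials to ensure blinding of the investigators and staff responsible for follow-up data collection" (analysis staff are named too), with the scope "to participant treatment assignments throughout the trial".
- **Data Management.** "Research assistants (blinded to treatment assignment) will review participant responses on questionnaires with participants present". The section then provides for gaps and errors found in that review: "skipped or incorrectly addressed items will be brought to the participant to correct". No questionnaire is excluded from this step.
- **Table 2 and its footnote 1.** The "Unified Theory of Acceptance and Use of Technology" instrument is marked at months 3, 6 and 15, with the note "Questionnaire administered to participants in the SM and CM interventions only".
- **Potential Mediators.** The instrument has been adapted to ask how SM and CM participants accept and use the online support systems that belong to those two interventions.

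The Data Analysis section makes UC the comparator for both primary comparisons of BMI at 15 months.

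**The concern.** The blinding promise and the assessment schedule do not fit together. An assistant who checks a participant's questionnaires for skipped items has to know which ones were due. When one of them is due only in SM and CM, and is about those interventions' online tools, the assistant learns whether the person is in UC simply by doing the job described.

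What is at stake is a stated safeguard for the comparison that matters most. UC is in both primary contrasts, so recognising UC is enough to weaken the blinding of both, even though SM and CM cannot be told apart this way. The nearest exposure is in the patient-reported secondary outcomes (SF-12, PHQ-9, Depression Anxiety Stress Scale). They are on the same list of questionnaires, so the person asking the participant to complete or correct answers may already know the arm. Weight on a balance beam scale and waist by tape also leave some room for the reader, but the article does not show that the same staff take them.

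**Working it through.** The plan gives no figure on this point, and its power calculation plays no part in it. The check sets the statements side by side.

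**Step 1: who must stay blinded, and for how long.** Investigators and staff responsible for follow-up data collection and analysis, for the whole trial (Randomization and Blinding).

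**Step 2: who sees the questionnaires.** Research assistants described as blinded, with the participant in the room, checking for skipped or wrongly answered items (Data Management). No instrument is exempted or given to other staff.

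**Step 3: which questionnaires differ by arm.**

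| Follow-up | UC | SM | CM |
|---|---|---|---|
| Month 3 | not given | given | given |
| Month 6 | not given | given | given |
| Month 15 | not given | given | given |

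Source: Table 2 and footnote 1. This is the only instrument in Table 2 with an arm restriction.

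**Step 4: what the assistant can infer.** Questionnaire present means SM or CM; absent means UC. With a target of 240 allocated 1:1:1, that is 240/3 = 80 UC participants separated from 240 − 80 = 160 intervention participants. With the planned maximum loss of 20%, the month-15 split would be about 80 × 0.8 = 64 against 160 × 0.8 = 128. The inference is direct for any participant whose questionnaires the assistant reviews.

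**Step 5: whether it spreads beyond the reviewer.** This depends on what the sentence about labels means.

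- *Reading A:* wherever an arm is mentioned in study material, a letter replaces its name. Individual assessment forms carry no letter. The disclosure then stays with the assistant who sees the questionnaires, one participant at a time.
- *Reading B:* participant-level documents carry the letter of that participant's arm. Because there is one letter per arm and not one code per person, a few month-3 reviews show which letter is UC. All of the roughly 80 people with that letter are then identifiable to anyone who handles labelled documents.

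The wording allows either reading. Steps 1 to 4 hold under both; only the spread in step 5 needs reading B.

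**Step 6: whether it reaches the primary outcome.** Primary and Secondary Outcomes describes how height and weight are measured but not by whom. Retention speaks only of assessment staff. Neither section, nor Data Management, gives the order of measurement and questionnaire review within a visit. The path from the questionnaire to the weight reading is therefore open but not established.

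**The case against.** The strongest reply is that a journal article condenses a manual of operations. Questionnaires run in survey software with real-time missing-value checks, so this one may already be completed away from the blinded assistants. The lack of a written exemption is weak evidence that none exists. That is fair as to practice. It does not remove the conflict, because the article does more than stay silent: it states a general review by blinded staff and a questionnaire schedule that defeats the blinding in that review.

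Three stronger readings are tempting, and the text does not support them.

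- *That the whole UC arm is certainly unblinded through its letter.* This needs reading B of the label sentence, which is possible but not stated.
- *That the people who weigh participants know the arm.* The article does not say that the reviewing assistants take weight, waist or blood pressure, nor that review comes first. If weight is taken before review, the questionnaire cannot affect that visit's reading, although knowledge from month 3 could carry to later visits if the same staff see the participant again.
- *That the bias can be put in BMI units.* An assumed reading shift of 0.25 to 0.5 kg at an assumed height of 1.70 m gives 0.25/1.70² = 0.09 to 0.5/1.70² = 0.17 kg/m², but nothing in the article supports the shift. The scales are calibrated quarterly against standard weights, although that checks the instrument and not the reader. Laboratory outcomes are not open to this route.

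It is also true that participants in a lifestyle trial know their arm and may mention it, so removing this route will not guarantee blinding. Such remarks are incidental, however. This disclosure is built into the schedule, occurs at every follow-up and can be avoided.

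**Conclusion.** The point holds in a limited form. As written, the plan has blinded research assistants review a set of questionnaires whose composition tells UC from intervention at months 3, 6 and 15, which contradicts its promise of blinding throughout the trial. This rests only on taking the Data Management statement and Table 2 at their word.

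Spread to the whole UC arm of about 80 is conditional on arm labels appearing on participant-level documents. Exposure of the BMI measurement is conditional on who measures and when, neither of which is given. The size of any resulting bias cannot be obtained from the document. The plan should be changed because the safeguard concerns the comparator in both primary contrasts and the remedy is administrative; no bias has been demonstrated.

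**What to change.** 1. Deliver the technology acceptance questionnaire online, outside the blinded assistants' review, and rely on the automatic missing-value checks that the data entry systems already have. State this exemption in Data Management and in footnote 1 of Table 2.
2. Keep its data apart from blinded staff, including those doing the analysis, until outcome data are locked. An otherwise coded arm with no data on this instrument would identify itself.
3. Use participant ID only on assessment forms and screens, and merge the arm code at analysis. State this in Randomization and Blinding, so that the label sentence has only one reading.
4. Take weight, waist and blood pressure before any questionnaire review, and state who takes them.

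The cost is a change to survey scheduling and form templates, with no extra staff and no change to sample size, visits or outcomes. The downside is possibly a few more missing items on this questionnaire, which is a process measure and not an efficacy outcome.

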#### Primary and Secondary Outcomes

The primary outcome measure is the BMI. Height and weight, in light indoor clothes without shoes, are measured using a wall-mounted stadiometer and a balance beam scale, respectively. All scales are calibrated quarterly by trained study personnel using standard weights. BMI is calculated as the Quetelet index (kg/m^2^).

Secondary outcomes include glycemic control and component risk factors of the metabolic syndrome. Plasma glucose, total cholesterol, triglycerides, and high-density lipoprotein cholesterol (HDL-C) are measured after an overnight fast, and low-density lipoprotein cholesterol (LDL-C) is calculated by the Friedewald equation [28]. Hemoglobin A1c and CRP are also measured. Waist circumference is measured using a tape, according to a standardized protocol, in a horizontal plane around the abdomen at the level of the right iliac crest[29] Blood pressure is measured in the seated position after at least a five-minute rest. At the BV1, blood pressure is measured in both arms and the arm with the higher pressure is used for all subsequent blood pressure measurements. At each assessment visit, three blood pressure measurements are obtained with one-minute between measurements, using equipment and procedures that meet the American Heart Association's recommendations for blood pressure measurement in humans [30].

Additional secondary outcomes include generic and obesity-specific health-related quality of life and mental health. The 12-item Short Form Health Survey (SF-12) [31], a widely used quality of life instrument, is administered to evaluate changes in non-disease specific physical and mental health status. The Obesity-Related Problem Scale specifically measures the impact of obesity on psychosocial functioning. The eight-item scale has high internal reliability and sound test--retest reliability, correlates strongly with a wide range of theoretically related constructs, and is responsive to weight loss intervention [32]. The nine-item Patient Health Questionnaire (PHQ-9) refers to the previous two-week interval and consists of nine items of depression symptoms and one follow-up question on functional impairment [33]. The PHQ-9 is both a measure of depressive symptomatology and a tentative diagnostic instrument for the *Diagnostic and Statistical Manual of Mental Disorders*, 4^th ^edition (DSM-IV) depressive disorders [34]. The 21-item Depression Anxiety Stress Scale has high internal consistency and correlates strongly with other validated self-report measures of depression, anxiety, and stress [35].

Furthermore, changes in diagnoses, medication use and health care utilization will be assessed. With participant authorization, data are extracted from their EHRs at baseline and again at 15 months on current medical problems, current prescription medications, and health care contacts during the study (including outpatient visits, ER visits, hospitalizations, and phone/email consultations). Pharmacy dispensing data are currently available for patients with capitated insurance only (making up about 30% of the PAMF patient population). While the vast majority of health care of PAMF primary care patients, including specialist care, is received from PAMF, a significant proportion of medications prescribed are not obtained from the PAMF pharmacy. Also, PAMF patients may seek care outside the system. Therefore, additional data are obtained on medication and supplement use by recording information from the container and on health care outside PAMF by participant self-report.

#### Potential Mediators

Data are also obtained on a battery of behavioral and psychosocial measures using existing self-report instruments to assess potential mediators of the interventions.

The two main foci of the SM and CM interventions are dietary changes to achieve weight loss and increased physical activity. Adherence to the interventions is assessed by three-day food records and the Stanford 7-Day Physical Activity Recall. Multiple-day food records are considered a gold standard for collection of individual dietary data [36]. The Stanford 7-Day Physical Activity Recall has been tested for validity and reliability [24] and is sensitive to change in physical activity [37,38]. In addition, adherence to the overall intervention "process" is assessed by documenting attendance at group sessions, completion of self-monitoring records, and frequency of use of the online self-management support systems included in the SM and CM interventions. Self-monitoring data obtained during the intervention program also are used for adherence monitoring and for individual feedback.

Based on the social cognitive theoretical underpinnings of the intervention (see below), two main hypothesized mediators of the intervention are selected to be measured: self-efficacy and social support. The Eating Habits Confidence Survey and the Exercise Confidence Survey [39], and the Social Support and Eating Habits Survey and the Social Support and Exercise Survey [40], have been shown to be reliable and have high internal consistency and are associated with other measures of social support and self-efficacy related to physical activity and dietary behaviors.

The questionnaire created by Venkatesh et al. [41] based on the Unified Theory of Acceptance and Use of Technology, a technology acceptance model, is adapted to assess user acceptance and use of the online self-management support systems among SM and CM intervention participants. The questionnaire includes the following scales: Performance Expectancy, Effort Expectancy, Social Influence, Facilitating Conditions, Attitude toward use, Self-Efficacy, Anxiety and Behavioral Intention.

#### Additional Process Measures

Data on the proportion and representativeness of patients willing to participate, as well as reasons for declining to participate, are used to assess the potential reach of the E-LITE interventions. Demographic and professional characteristics of PCPs (e.g., age, sex, years in practice, specialty and board certification, PAMF department, panel size and composition, %FTE) are obtained from PAMF administrative records. Data on the proportion and representativeness of physicians willing to approve their potentially eligible patients for participation are used to assess the likelihood of adoption of the E-LITE interventions.

### Interventions

#### Theoretical Basis

The theoretical underpinning of the E-LITE interventions is derived from Social Cognitive Theory [42] and the Transtheoretical Model of Behavior Change [43]. The former emphasizes the reciprocal determinism between individual, environment, and behavior, whereas the latter recognizes that behavior change is a dynamic process that moves, at variable speed, through varying stages of readiness to change. Behavior change is more likely with increased behavior capability, and behavior capability is strengthened through goal setting, skill building and self-monitoring. Also important are confidence in one's ability to perform a given behavior (self-efficacy) and expectation of favorable outcomes of the behavior (outcome expectations). Behavioral strategies may vary by stage of change (i.e., experiential processes during initial phases of behavioral adoption and behavioral processes occurring during action and maintenance phases) [43]. In addition, the E-LITE interventions draw upon key research evidence for the importance of self-management in chronic disease management [44-46]. Successful self-management intervention is driven by patient-defined problems and fosters the mastery of skills in problem solving, action planning, decision making, and support building through an iterative process [46,47].

This theoretical basis distinguishes the E-LITE interventions from the delivery of lifestyle modifications in the usual primary care setting. Current practice routinely involves physician advice, occasionally with referral to a dietitian who takes a diet history and who then provides standard educational materials and advice during a small number of individual or group sessions, typically with little or no follow-up. This standard clinical approach lacks the theoretical basis and behavioral self-management focus described above.

#### Evidence-based Intervention Goals

A goal-based approach is used in both SM and CM interventions, in which participants are given the same general goals: 7% weight loss and 150 minutes of moderate physical activity per week. These goals are consistent with those of the DPP [7]. Participants who wish to lose more than 7% of their starting weight may be encouraged to do so only insofar as the participant maintains a normal BMI at or above 21 and the rate of weight loss does not exceed three pounds per week. The physical activity goal is consistent with the new Physical Activity Guidelines for Americans [48], and is deemed safe and attainable for most adults. Participants, especially those who are habitually sedentary, are advised to gradually and steadily increase their activity level and reach the goal within five weeks of beginning activity, or as soon as possible thereafter. Regular physical activity recommendations for activities of moderate intensity other than brisk walking, as well as strength and flexibility physical activities, are to be tailored to participant situation [49,50]. After attaining the minimum goal of 150 minutes a week, participants who wish to be more active are encouraged to do so, as tolerated. If participants reach the 150-minute goal but are not achieving the weight goal, they are encouraged to further gradually increase their physical activity to 60 minutes/day of moderate physical activity [49,51,52]. Participants in both SM and CM interventions are strongly encouraged to track their weight and physical activity using the American Heart Association's online self-management portal at http://www.heart360.com.

Recommendations are also given for total fat reduction (to 25% of calories from fat) and calorie balance and restriction (with a goal of a 500- to 1000-calorie reduction diet). As in the DPP [7], the calorie and fat goals are given as a means to achieve and maintain the weight goal, rather than as a goal in and of itself. Therefore, if a participant consumes more than the assigned calorie or fat goal, but is achieving the weight goal, there is no need to focus on further reductions. Portion control, choices of low-energy and nutrient-dense meals and snacks, healthy food preparation techniques, and careful selection of restaurants, including fast food, and the items offered are promoted as strategies to gradually achieve the calorie and fat goals. Participants also are recommended to (1) lower saturated fat intake to < 10% of caloric intake, (2) lower cholesterol intake to < 300 mg/day, (3) consume a high plant-based diet that includes a variety of fruits and vegetables, whole grains, and low-fat dairy products, and (4) reduce intake of high glycemic index carbohydrates.

